**Information’s about adverse reactions:**

| **Start date** | **Duration or end date** | **Severity (mild, moderate, severe)** | **Relationship with the product (possible related; unrelated; unknown)** |
| --- | --- | --- | --- |
|  |  |  |  |

**Describe the adverse reaction in details: ______________________________________________________________________________________________________________________________________________________________________________________________________________________________________________________________**

**Regarding the adverse reaction, answer:**

( ) Resolved – Date:____/____/______

( ) Resolution process

( ) Unknown/Lost to follow-up

( ) Not solved

( ) Resolved with sequel

( ) Other: ________________________

**Action performed with the test product:**

( ) Continued use

( ) Stopped use

( ) Stopped use temporarily

( ) Reduced use, specify:_____________________________________________

( ) Unknown

( ) Other

**Did the adverse reaction decrease after stopping or reducing the dose of the product?**

( ) Yes No

**Did the adverse reaction reappear after reintroducing use of the product?**

( ) Yes No

**Participant protocol status:**

( ) Continuous protocol

( ) Discontinuous protocol

**Treatment for adverse reaction/serious adverse reaction:** ____________________________________________________________________________________________________________________________________________

**Relevant medical history data:**

( ) Yes, list them ( ) None ( ) Not provided ( ) Unknown

- Medical history, with start date, if known: ______________________________________________________________________

**Relevant concomitant medications:**

( ) Yes, list them ( ) None ( ) Not provided ( ) Unknown

- Medication name, dose, frequency, medication start and stop dates or

duration of therapy if known is: _____________________________________________________________________

**Relevant laboratory data:**

( ) Yes, list them ( ) None ( ) Not provided ( ) Unknown

- Laboratory test, results and dates if known: ______________________________________________________________________

Date: ______/______/_________

Signature of the examining dentist: __________________________________________

**APPENDIX C – HEALTH QUESTIONNAIRE**

**Date: ____/____/_______ Number of Participant:** ___________________

**Birthday date: ____/____/_______** Skin color: ______________________

**Telephone:**

**Smoker:** ( ) Yes ( ) No ( ) Ex-smoker

**MEDICAL HISTORY**

**Doctor’s name: _________________________________________________________**

**Doctor’s telephone: _____________________________________________________**

**Date of the last visit to the Doctor: _________________________________________**

**Name of an emergency contact: ___________________________________________**

**Telephone of an emergency contact: _______________________________________**

**Current condition of your systemic health is:** ( ) Good ( ) Regular ( ) Bad

**Have you ever undergone a serious surgery procedure?** ( ) Yes ( ) No

**If yes, explain: _________________________________________________**

**Are you doing any medical treatment?** ( ) Yes ( ) No

If yes, explain: __________________________________________________

**This year (2022), have you been vaccinated against common flu (Influenza)?** ( ) Yes ( ) No

Have you been vaccinated against **SARS-CoV-2 (Covid-19)?** ( ) Yes ( ) No

Have you ever been treated or diagnosed with any of these conditions?

( ) Abnormal bleeding

( ) Hemophilia

( ) Blood transfusion

( ) Ulcer/Colitis

( ) Heart problems

( ) Epilepsy/fainting

( ) Asthma

( ) Arthritis

( ) Glaucoma

( ) Drug abuse

( ) Skin problems

( ) Blood diseases

( ) Chemotherapy/Radiotherapy

( ) Diabetes/Abnormal blood sugar

( ) Breathing difficulties

( ) Lung problems

( ) High or low blood pressure

( ) Anemia

( ) AIDS

( ) Cancer/Tumor

( ) Kidney or liver disease

( ) Hepatitis/Jaundice

( ) Emphysema

( ) Rheumatic fever

Please, describe the conditions cited above: __________________________________________________________________________________________________________________________________________________________________________________________________________________

Height:______ Weight: _______ Blood pressure: _________

Are you allergic to any oral care product, personal hygiene product, or any of its ingredients? ( ) Yes ( ) No

If there is, explain: ____________________________________

Do you use any medication daily?

| **Name of the medication** | **Dose** | **Daily frequency** | **Reason** |
| --- | --- | --- | --- |
|  |  |  |  |
|  |  |  |  |
|  |  |  |  |
|  |  |  |  |
|  |  |  |  |

**DENTAL HISTORY**

**Dentist’s name: _________________________________________________________**

**Dentist’s telephone: _____________________________________________________**

**Date of the last visit to the Dentist: ________________________________________**

**What is the frequency that you visit your dentist: ____________________________**

**Telephone of an emergency contact: _______________________________________**

**JUST FOR WOMEN**

You are pregnant? ( ) Yes ( ) No If so, for how many months? _____________

Are you currently breastfeeding? ( ) Yes No

**APPENDIX D – SOFT AND HARD ORAL TISSUE EXAMINATION FORM**

**Number of participant: Date: _/ __/**________

What is the experimental period of this evaluation: ( ) Baseline ( ) 30 days ( ) 90 days

| Area | Normal | |  | |
| --- | --- | --- | --- | --- |
| 1. Soft palate | Yes ( ) | No ( ) | |  |
| 2. Hard palate | Yes ( ) | No ( ) | |  |
| 3. Gingival mucosa | Yes ( ) | No ( ) | |  |
| 4. Oral mucosa | Yes ( ) | No ( ) | |  |
| 5. Mucogingival folds | Yes ( ) | No ( ) | |  |
| 6. Tongue | Yes ( ) | No ( ) | |  |
| 7. Sublingual and submandibular areas | Yes ( ) | No ( ) | |  |
| 8. Salivary glands | Yes ( ) | No ( ) | |  |
| 9. Tonsillar and pharyngeal areas | Yes ( ) | No ( ) | |  |

If any of your responses it’s a No, explain: ____________________________________________________________________________________________________________________________________________

Date: __/__/__ Signature of the examiner dentist:

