4.4.2. Soft and hard oral tissue exams

All individuals will receive an examination of the soft and hard oral tissues. This exam will be performed by a single trained and calibrated examiner. With the aid of an odontoscope and artificial lighting from the dental chair, the examination will include an evaluation of the hard and soft palate, gingival mucosa, buccal mucosa, mucogingival areas, tongue, sublingual and submandibular areas, salivary glands and tonsillar, and pharyngeal areas. Findings will be recorded on the Soft and Hard Tissue Examination Form (Appendix D). If necessary, individuals will be immediately referred to the Stomatology Service of the Faculty of Dentistry at Federal University of Pelotas.

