## **5.2. Risks and benefits**

In general, it is not expected that there will be any side effects from the use of any of the products under test, considering that they are products in routine use and commercially available. However, there is the possibility of soft tissue irritation or temporary tooth sensitivity with the use of these products, as with any oral hygiene product that is regularly used. When these conditions occur, it is recognized that they disappear with the suspension of use of the product. The oral tissue examination, which will be performed, is used as part of routine oral health care. There is also a risk of discomfort when answering the questionnaire questions. Participants will need to spend time traveling and participating throughout the study period, in addition to the need to purchase a mobile data package for the weekly questionnaires sent out. Because of this, patients will be compensated with the amount of R$50.00 (fifty Brazilian Reais), for each visit carried out, in order to offset the expenses inherent to their travel to the Faculty of Dentistry at Federal University of Pelotas. In addition, the purchase of the mobile data package will also be reimbursed with the amount of R$100.00 (one hundred Brazilian Reais) during the participants' last return.

No direct benefits are expected from participating in this study. The results of the study may help to find alternative methods to reduce the occurrence of flu and cold symptoms. Additionally, help ensure that the product is safe to market to the public. The research team will be responsible for dealing with adverse events arising from participation in the study.

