# **ADVERSE EVENTS**

## **Definitions**

Adverse events (AEs) and serious adverse events (SAEs) are defined by the Good Clinical Practice Guidelines as follows:

**Adverse events:** Any unconventional medical occurrence in a patient or in clinical research participants who are receiving administration of a pharmacological agent and which does not necessarily need to have a causal relationship with the treatment. An adverse event can, therefore, be any unfavorable and unintended sign (including abnormal laboratory findings), symptoms or temporary illnesses associated with the use of medicinal products, whether or not related to the medicinal product.

AEs include any sign of deterioration in a participant's medical status after being enrolled in a study. AE can involve any organ or system that can be represented by the new occurrence or deterioration of the disease, a syndrome, a symptom, a physical sign, as well as by findings and results of instrumental examinations and laboratory tests. Any inconvenient change since the subject's inclusion, occurring after the first administration of the study test product, is considered an adverse effect. All such occurrences must be recorded and reported appropriately, whether they are related to the study medication or not.

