# **APPENDIX H – VISIT FORM**

Participant number: Date: __/__/__

Is the patient currently taking any medication? (including over-the-counter products)

( ) Yes No ( )

In affirmative case, list all medications:

| **Medication** | **Total daily dose** | **Start date** | **End date (circle the “C” in case of a medication for continuous use** | **Indication** |
| --- | --- | --- | --- | --- |
|  |  |  | **C** |  |
|  |  |  | **C** |  |
|  |  |  | **C** |  |
|  |  |  | **C** |  |

All medications must be reviewed by the study supervisor.

1. Have there been any unexpected or serious reactions since the previous exam? ( ) Yes No ( )

2. For the condition mentioned above, was there any treatment prescribed? ( ) Yes No ( ) ; If yes, please describe: ______________________________________________________________________

3. Has any dental treatment been performed since the previous examination? ( ) Yes No ( );

If yes, please describe: ______________________________________________________________________

4. Since the last exam, have any medications been prescribed? ( ) Yes No ( );

If yes, describe dose, duration and reason: ______________________________________________________________________

5. Is the volunteer pregnant or breastfeeding? ( ) N/A ( ) Yes ( ) No

6. Do any of the answers to questions 1 to 5 justify the exclusion of the participant's data from the statistical analysis? ( ) Yes No ( );

If yes, please explain: ______________________________________________________________________

7. Will the participant continue in the study? ( ) Yes No ( )

If the answer to question 7 is “No”, complete question 8.

8. Did the participant complete the entire study? ( ) Yes No ( )

If not, please explain: ____________________________________________________________________________________________________________________________________________

Date: ______ Signature of the examining dentist: ______________________________

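### The only scheduled adverse-event question is narrower than the protocol's own recording rule, and no scheduled form prompts for tooth sensitivity, so capture of mild foreseen effects may be incomplete

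*Combined protocol and SAP*

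**What the plan says.** **Named effects.** Section 5.2 (Risks and benefits) says that "there is the possibility of soft tissue irritation or temporary tooth sensitivity with the use of these products", and that such effects go away when use stops.

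**Recording rule.** Section 8.1 (Definitions) treats any untoward change as an adverse effect if it is one "occurring after the first administration of the study test product, is considered an adverse effect" in the protocol's terms. It adds: "All such occurrences must be recorded and reported appropriately, whether they are related to the study medication or not". Section 8.3 sends every complaint, symptom or sign meeting the definition to Appendix B.

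**Oral examination.** Appendix D is titled "SOFT AND HARD ORAL TISSUE EXAMINATION FORM". Its rows include "3. Gingival mucosa" and end at "9. Tonsillar and pharyngeal areas". Each is marked normal or not, with free text for any abnormal finding. Section 4.4.2 gives the matching list: "the examination will include an evaluation of the hard and soft palate, gingival mucosa, buccal mucosa, mucogingival areas, tongue", followed by the sublingual, submandibular, salivary gland, tonsillar and pharyngeal areas. Teeth appear in neither list.

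**Visit question.** Appendix H, completed at days 30 and 90, asks in question 1: "Have there been any unexpected or serious reactions since the previous exam". It does not refer to Appendix B.

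**Visit sequence.** Section 5.3 lists Appendices D and H for both follow-up visits, plus the completed daily logs at day 90. Appendix B is not in that sequence.

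**The concern.** The protocol sets a broad rule for what must be recorded, then gives the examiner a narrow question with which to find it. The two effects it foresees are the ones most likely to fall outside that question: both are mentioned in advance, and neither is serious when mild. Tooth sensitivity has no examination row as a second route.

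What is at stake is how far the harms data can be relied on. The Abstract says adverse events are collected throughout the study, and section 5.2 says the results may help show that the product is safe to market. A low count that depends largely on what participants choose to mention is weak support for that. Control participants receive no mouthwash, so participants know whether they are gargling. Unprompted reporting could therefore differ between arms, in either direction.

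**Working it through.** No formula applies and the plan gives no figure to reproduce. The check matches each effect named in section 5.2 against each form that could capture it.

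| Form | Tooth sensitivity | Soft-tissue irritation |
| --- | --- | --- |
| Appendix D (baseline, day 30, day 90) | No row: 0 of 9 | Several mucosal rows with free text, if visible on the day of the exam |
| Appendix H, question 1 | Not prompted if mild and regarded as foreseen | Not prompted if mild and regarded as foreseen |
| Appendix H, questions 2 to 5 | Reached only indirectly, through treatment or medication | Same |
| Appendix F (daily log) | No item | No mouth item; throat soreness and scratching are logged as cold symptoms |
| Appendix B | Can be recorded | Can be recorded |

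The counts that follow are:

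- Named effects that can be recorded on Appendix B: 2 of 2. Its description is open and its severity scale starts at mild.
- Named effects with a structured examination item: 1 of 2 (irritation yes, sensitivity no).
- Named effects, when mild, that question 1 prompts for if anything foreseen in section 5.2 counts as expected: 0 of 2.

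**Timing.** The follow-up examinations are 90 − 30 = 60 days apart. Irritation that arises and resolves within that interval leaves nothing to see at day 90. Question 1 does cover the whole interval, since it runs from the previous exam, but it reaches such an episode only if read broadly.

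**Rule against prompt.** Section 8.1 has no filter for expectedness or seriousness; question 1 has both. An examiner who follows question 1 literally can complete the visit forms in full and still leave unrecorded an event that sections 8.1 and 8.3 require on Appendix B.

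**The case against.** The strongest reply is that the designated form is adequate and the rule is complete. Appendix B takes mild events, section 8.3 requires all qualifying complaints to be entered there, and the examining dentist who signs Appendix H works under that rule. This stands as far as it goes. A reader might infer that the forms cannot record the named effects. The documents do not support that: both can be entered on Appendix B, and Appendix D examines directly for soft-tissue irritation.

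Second, section 5.2 also says that side effects are in general not anticipated. On that wording, any reaction could be called unexpected and question 1 would catch it. The protocol never defines the term, so this reading is open. It shows that the question is ambiguous, not that it is sufficient, and two examiners could apply it differently.

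Third, there are other routes. Labels carry an emergency contact, Appendix H asks about dental treatment and medication, and the consent form (Appendix A), which was not available for this check, may tell participants to report reactions. It therefore cannot be said that spontaneous mention at a visit is the only route. These routes do not prompt for a mild effect that needed no treatment.

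Fourth, tooth sensitivity is mainly a reported symptom, so its absence from an inspection checklist is not in itself a safety gap. This is fair, and it is why the visit question matters more than the missing row.

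Finally, safety is not part of the stated aim and section 4.7 specifies no safety analysis. This limits the weight of the point but does not remove the recording duty in section 8.

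**Conclusion.** The point holds as a mismatch between prompt and rule. The only scheduled adverse-event question is narrower than sections 8.1 and 8.3, no scheduled form prompts for tooth sensitivity, and irritation that resolves between the day 30 and day 90 exams is asked about only on a broad reading of that question. Mild foreseen effects may reach Appendix B only if volunteered, so capture may be incomplete.

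A reader might go further and infer that harms will be under-counted, or attach a number. The documents support neither. They give no expected adverse-event rate and no detection rate. The usual bound for zero recorded cases, 3/75 = 4% with all test participants or 3/60 = 5% with the 60 per group in the sample-size section, assumes that every case is detected. It says nothing about how many are missed.

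The conclusion assumes that question 1 is applied as written and that effects foreseen in section 5.2 are treated as expected. The primary outcome and the sample size are unaffected. This is a cheap improvement to safety data collection.

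**What to change.** Reword Appendix H question 1 along these lines: *Has there been any adverse event since the previous exam, expected or not, serious or not, including mouth or throat irritation and tooth sensitivity?* Add an instruction that a positive answer requires Appendix B to be completed, and list Appendix B, where applicable, in the visit sequence of section 5.3.

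Optionally, add a row for teeth to Appendix D and to the examination list in section 4.4.2, so that the content matches the form's title.

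The cost is a few text edits, with no extra visit or staff. The downside is a few more minor events to record.

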# **APPENDIX E – INITIAL EXAM FORM**

**Number of participant: ___________ Age: ________Date: ____/____/____**

1. Is the participant between 18 years old and 70 years old? ( ) Yes No

2. Is the participant available to participate in the entire study? ( ) Yes No

3. Does the participant have good systemic health? ( ) Yes No

4. Is the participant willing to provide information related to their medical history?

( ) Yes ( ) No

1. Did the participant sign the informed consent form? ( ) Yes No

**If, for questions 1 to 5, there is a “no” answer, the participant is ineligible for the study. He should be dismissed, and question 14 should be completed. If the subject is eligible, complete questions 6-13.**

6. Is the participant participating in another clinical trial or has participated in a clinical trial in the last month? ( ) Yes ( ) No

7. Is the participant pregnant or breastfeeding? ( ) Yes ( ) No

8. Does the participant have a history of allergies to oral hygiene products, personal hygiene products, or their ingredients? ( ) Yes ( ) No

9. Does the participant currently have mouth irritation or use oral anesthetics?

( ) Yes ( ) No

10. Does the participant have diabetes? ( ) Yes ( ) No

11. Is the participant immunocompromised (HIV, AIDS, immunosuppressive drug therapy)? ( ) Yes ( ) No

12. Does the participant use complete dentures? ( ) Yes ( ) No

13. Does the participant have carpal tunnel syndrome or arthritis in the hands?

( ) Yes ( ) No

**If, for questions 6 to 13, there is a “yes” answer, the participant is ineligible for the study. He should be dismissed, and question 14 should be completed.**

14. Is the subject eligible to enter the study? ( ) Yes No ( )

Date: ________ Signature of the examining dentist: _______________________

**APPENDIX F – DAILY LOG QUESTIONNAIRE**

| **Wisconsin Survey of Upper Airway Respiratory Symptoms (WURSS-21) - Symptom Diary** |
| --- |
| Day: Date: Hour: ID: |

**Fill in ONE circle for each of the following:**

|  | I don’t feel Sick  **0** | Very lightly  **1** | **2** | Lightly  **3** | **4** | Moderately  **5** | **6** | Seriously  **7** |
| --- | --- | --- | --- | --- | --- | --- | --- | --- |
| How sick do you feel today? |  |  |  |  |  |  |  |  |

**Rate the average severity of each cold symptom over the past 24 hours:**

|  | Don’t have this symptom  **0** | Very light  **1** | **2** | Light  **3** | **4** | Moderate  **5** | **6** | Serious  **7** |
| --- | --- | --- | --- | --- | --- | --- | --- | --- |
| Runny nose |  |  |  |  |  |  |  |  |
| Stuffy nose |  |  |  |  |  |  |  |  |
| Sneeze |  |  |  |  |  |  |  |  |
| Sore throat |  |  |  |  |  |  |  |  |
| Throat scratching |  |  |  |  |  |  |  |  |
| Cough |  |  |  |  |  |  |  |  |
| Hoarseness |  |  |  |  |  |  |  |  |
| Pressure in the head |  |  |  |  |  |  |  |  |
| Pressure in the chest |  |  |  |  |  |  |  |  |
| Tiredness |  |  |  |  |  |  |  |  |

If you have experienced at least ONE of the symptoms above, respond below:

- In the last 24 hours, how much did your cold interfere with your ability to:

|  | No way  **0** | Very lightly  **1** | **2** | Lightly  **3** | **4** | Moderately  **5** | **6** | Seriously  **7** |
| --- | --- | --- | --- | --- | --- | --- | --- | --- |
| Think clearly |  |  |  |  |  |  |  |  |
| Sleep well |  |  |  |  |  |  |  |  |
| Breathe easily |  |  |  |  |  |  |  |  |
| Walking, climbing stairs, exercising |  |  |  |  |  |  |  |  |
| Perform daily activities |  |  |  |  |  |  |  |  |
| Working outside home |  |  |  |  |  |  |  |  |
| Working inside home |  |  |  |  |  |  |  |  |
| Interact with people |  |  |  |  |  |  |  |  |
| Live your personal life |  |  |  |  |  |  |  |  |

- Compared to yesterday, I feel that my cold is:

| Much better | Better | A little better | Same | A little worst | Worst | Much worst |
| --- | --- | --- | --- | --- | --- | --- |
|  |  |  |  |  |  |  |

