Other studies have been carried out and sought to evaluate the potential of solutions used locally in the mouth/oropharynx region in the context of viral infections. In an *in vitro* study, using two commercially available toothpastes and two mouthwash solutions, it was observed that rinsing with hydrogen peroxide, or with cetylpyridinium chloride, or using toothpastes with stannous fluoride had important antiviral effects (RAMJI, CIRCELLO, WINSTON, et al., 2022).

Cetylpyridinium chloride (CPC) is a quaternary ammonium compound, with high safety and widespread use as an adjunct to oral hygiene procedures. It has good adherence by patients, and its antibacterial effect on the oral microbiota is undisputed (LANGA, MUNIZ, COSTA, et al., 2021). Furthermore, recently, the literature has demonstrated that the addition of zinc (Zn) to mouthwashes containing CPC has demonstrated superior clinical effects when compared to mouthwashes containing only CPC (RÖSING, CAVAGNI, GAIO et al., 2017) or essential oils (LANGA, CAVAGNI, MUNIZ et al., 2021). However, its antiviral potential is still little tested, but it has potential and has been recommended as a pre-operative mouthwash for dental procedures (RETAMAL-VALDES, SOARES, STEWART, et al., 2017).

Based on these potentials and the need for clinical studies, in addition to the possible effect of the topical use of oral antiseptics to reduce viral infections, this study is justified, which aims to evaluate the effect of using a CCP+Zn solution in the form gargling when flu and cold symptoms occur. The hypothesis under study is that the local presence of CCP+Zn can reduce the occurrence of flu-like symptoms when compared to the absence of these active ingredients.

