# **AIM**

The aim of this study will be to evaluate the efficacy of regular cleaning of the oropharynx, on the incidence and duration of symptoms associated with flu and colds, with the use of CCP+Zn gargling compared to the absence of gargling.

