### Sample size

The sample size of 150 individuals (75 per group) was based on internal data from the sponsor of this study. It was determined that 60 individuals per group are needed for 80% power for the occurrence of flu-like symptoms. Considering the nature of the study and the demand for daily questionnaire responses, an attrition rate of 25% is assumed over the course of the study.

- - 1. Inclusion criteria

Individuals must meet all the following criteria:

1. Sign this informed consent form (ICF) (Appendix A);

2. Men or women, aged between 18 and 70;

3. Good systemic general health as determined by study investigators;

4. Availability of 90 days to participate in the study;

- - 1. Exclusion criteria

During the study, the following exclusion criteria will be considered:

1. Be participating in any other clinical study;

2. Being pregnant or breastfeeding;

3. Present a history of allergies to oral hygiene products, personal hygiene products, or their ingredients;

4. Have mouth irritation or use oral anesthetic sprays;

5. Have diabetes;

6. Be undergoing extensive dental treatment or oral surgery during the study;

7. Present immunocompromised (HIV, AIDS, immunosuppressive drug therapy);

8. Use complete dentures;

9. Have carpal tunnel syndrome or arthritis in the hands.

10. Participant who substantially fails to follow the required protocols;

11. Participant who fails to attend scheduled appointments;

12. Participant who is treated, during the study period, with medications that may interfere with the parameters being analyzed in the study;

13. Participant who is treated by a medical or dental service, and this may interfere with the parameters being analyzed in the study;

14. Participant who develops serious adverse reactions. The investigator will immediately record the information on the Adverse Reactions Form (Appendix B);

15. The participant who chooses to end their participation in the study;

16. Participant reports being pregnant during the study.

- 1. **Tests products**

Participants will be randomized into one of the following experimental regimens and will receive products as follows:

Group control:

● Colgate Maximum Cavity Protection® Toothpaste.

● Commercially available soft toothbrush.

Test Group:

● Mouthwash containing 0.075% CCP and 0.28% zinc lactate, in an alcohol-free base, commercially available in Brazil.

● Colgate Maximum Cavity Protection® Toothpaste.

● Commercially available soft toothbrush.

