## **4.7. Statistical analysis**

Chi-square test will be performed for gender data, and an independent t-test for the age variable, to test the hypothesis that the groups present balanced distribution of variables. The proportion of symptom-free days (i.e., none of the 10 symptoms were present) will be used for the primary outcome variable. Chi-square test will be used to compare the proportion of symptom-free days for the experimental groups. Analysis of variance can be used to compare groups. Significance level will be set at 95%.

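### The daily log asks only about upper-airway cold symptoms, so the systemic part of flu goes unmeasured and flu-like illness cannot be told apart from a cold

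*Combined protocol and SAP*

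**What the plan says.** The aim (Section 2) is to evaluate the effect of oropharyngeal cleaning "on the incidence and duration of symptoms associated with flu and colds". The operational hypothesis (Section 3) and the design statement (Section 4.1) also take flu and colds together. Two places are narrower. The introduction's hypothesis is that the product "can reduce the occurrence of flu-like symptoms when compared to the absence of these active ingredients", and the sample size section says: "It was determined that 60 individuals per group are needed for 80% power for the occurrence of flu-like symptoms". Neither place defines flu-like symptoms.

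Section 4.4.1 presents the Appendix F log as the daily record of flu and cold symptoms. The log itself is headed "Wisconsin Survey of Upper Airway Respiratory Symptoms (WURSS-21) - Symptom Diary". It opens with one general rating from 0 to 7, "How sick do you feel today", and then gives the instruction "Rate the average severity of each cold symptom over the past 24 hours" above ten items. A further instruction, "If you have experienced at least ONE of the symptoms above, respond below", leads to nine interference items and one better-or-worse item, both worded about a cold.

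Section 4.7 builds the primary outcome on the ten items alone: "The proportion of symptom-free days (i.e., none of the 10 symptoms were present) will be used for the primary outcome variable".

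**The concern.** The trial describes itself as a study of flu and cold symptoms, with influenza as its first key word, but the instrument behind the primary outcome is a cold survey. It has no item for fever, chills or muscle or body ache, the systemic symptoms that ordinarily mark a flu-like illness.

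Two things are at stake. A day with only those symptoms would be scored symptom-free. And because the systemic symptoms are never asked about, no later analysis can count flu-like days or affected participants by arm. A positive result could then be reported as a reduction in flu symptoms when participants were asked only about a cold, and a null result would say nothing about flu-like illness as such.

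**Working it through.** **Step 1. What the log contains.** Count the items in Appendix F: 1 general rating + 10 symptoms + 9 interference items + 1 better-or-worse item = 21. The ten symptoms agree in number with the ten in Section 4.7, so the outcome and the form are consistent with each other.

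**Step 2. The ten items against the construct.**

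| Area | Items in Appendix F | Number |
|---|---|---|
| Nose | runny, stuffy, sneezing | 3 |
| Throat and voice | soreness, scratching, hoarseness | 3 |
| Cough | cough | 1 |
| Pressure | head, chest | 2 |
| General | tiredness | 1 |
| Fever, chills, muscle or body ache | none | 0 |

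The total is 10, with 0 of 10 for the systemic symptoms. The only general item is tiredness.

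**Step 3. Could another part of the documents fill the gap?**
- The general sickness rating is answered every day, but it names no symptom and is not part of the primary outcome.
- The interference items are answered only if one of the ten symptoms is present, so they cannot recover a day on which all ten are zero.
- The Adverse Reactions Form (Appendix B) has a free-text description, and the Visit Form (Appendix H) lists medications with their indication. Either might mention a fever. Neither asks for one, neither is a daily record, and neither feeds the efficacy outcome.
- There is no temperature measurement, viral test or case definition of flu or flu-like illness.

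**Step 4. Does the power statement identify the outcome?** The plan's 75 per group follows as 60 x 1.25 = 75. The 60 itself cannot be reproduced, because no event rate, standard deviation or effect is given. At two-sided 0.05 and 80% power, without continuity correction, 60 per group fits several readings (control rates assumed): 0.30 against 0.097, 0.50 against 0.254, 0.70 against 0.449, 0.80 against 0.564, or a mean difference of about 0.51 standard deviations. The figure therefore does not show whether it refers to participants with flu-like symptoms or to the proportion of symptom-free days.

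**Step 5. Size of the error in the primary outcome.** Let f be the share of diary days with flu-like illness and m the share of those days with none of the ten symptoms. The overstatement of the symptom-free proportion is f x m. The documents give neither value. With m assumed at 0 to 10%, the error lies between 0 and 0.10f. It applies to at most 150 x 90 = 13,500 diary days.

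**Step 6. Pessimistic illustration by participant.** Suppose the outcome were the occurrence of illness per participant and a share m of affected participants were missed equally in both arms. With n = 60 per group and rates p1(1-m) and p2(1-m), normal approximation:

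power = Phi{[|difference| x sqrt(n) - 1.96 x sqrt(2 x pbar x qbar)] / sqrt(p1q1 + p2q2)}

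| m | 0.50 v 0.255 | 0.60 v 0.35 |
|---|---|---|
| 0% | 79.8% | 79.0% |
| 5% | 76.4% | 75.0% |
| 10% | 72.8% | 70.7% |
| 20% | 65.1% | 61.9% |

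All rates and values of m are assumptions. The table probably overstates the loss, because a participant is missed only if none of the ten symptoms is scored on any day of the illness.

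**The case against.** The strongest defence is that the plan uses a named instrument whose ten items match the primary outcome exactly, and that the aim, operational hypothesis and design statement pool flu and colds. No endpoint calls for separating them. In the introduction and the sample size section, flu-like symptoms may be loose shorthand for the same pooled construct. That stands, and it means the primary comparison is not invalidated.

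A reader might infer that the trial cannot detect flu-like illness at all. The documents do not support that: cough, sore throat, head or chest pressure, or tiredness at any level makes the day symptomatic. Only a day with systemic symptoms and none of the ten is misscored.

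A reader might also infer that a stated flu question is left wholly unanswered. The plan poses no separate flu question, so what is lost is the ability to support flu-specific wording. Nor can it be said that nothing else records these symptoms. Adverse-event text may pick some up, although no form asks for them.

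A fair limit on the point itself is that the role of fever, chills and aches in marking flu-like illness is ordinary clinical knowledge and is not stated in the plan.

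What the defence does not answer is that the systemic part of flu symptoms lies within even the pooled aim, yet is not asked about. The power statement also rests on a term that neither the log nor Section 4.7 defines.

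**Conclusion.** The point holds as one of coverage and interpretation. The ten items that define the primary outcome include no fever, chills or muscle or body ache, and the collected data cannot identify flu-like illness apart from a cold. The direct bias in the symptom-free proportion is probably small: between zero and one tenth of the share of flu-like days, if 0-10% of those days show none of the ten symptoms. That range is an assumption with no figure in the documents behind it. A material loss of power might be inferred from the Step 6 table, but it is not established, since the rates there are assumed and the scenario is pessimistic.

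As designed, a result in either direction supports a statement about the ten listed upper-airway and cold symptoms. It does not support a statement about flu-like illness. The change is worth making because it is cheap and serves the trial's own flu-and-cold question.

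**What to change.** 1. Leave the WURSS-21 block and the ten-item primary outcome of Section 4.7 as they are.
2. After that block, add three separate daily yes/no lines: felt feverish or measured a fever; chills; muscle or body aches. They should be answered every day, whether or not any of the ten symptoms is present.
3. Pre-specify a definition of a flu-like day, for example feverishness plus at least one respiratory item. Report flu-like days and participants with any such day, by arm, as a secondary outcome with confidence intervals. The plan gives no event rate, so how informative this will be with 75 per group is unknown.
4. Pre-specify a sensitivity analysis of the primary outcome in which a day with any added symptom is not symptom-free. Keeping this out of the primary analysis avoids redefining the outcome.
5. In the sample size section, define flu-like symptoms. State that the 80% power refers to the Section 4.7 outcome only if the sponsor's internal data support that; otherwise name the outcome it does refer to.
6. If the log is already in use, limit the hypothesis and the conclusion to the ten listed upper-airway and cold symptoms.

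The cost is three tick lines per diary day, a reprint of the log, one secondary analysis and one sensitivity analysis. The downside is slightly more daily burden. Item 6 costs wording only. No extra visit, test or staff is needed.
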